**Preliminary Studies**

A retrospective chart review of pregnant women accessing prenatal care at SFGH Women’s Health Clinic (WHC) showed that due to the change in standard of care at SFGH, from a dedicated HIV counseling and testing service to provider-performed counseling and testing, prenatal HIV testing uptake at SFGH has increased from 52% in 2003 to 93% as of April 2006. In a cross-sectional study of prenatal patients at SFGH WHC, nearly 70% of women surveyed supported routine testing as compared to 27% who supported elective testing. This support for routine prenatal HIV testing was comparable to these women’s attitudes towards routine rubella screening (63% support) and routine gonorrhea/chlamydia screening (77% support). The study we propose would be the natural next step in more specifically evaluating the routinization and streamlining of HIV testing in the prenatal care setting through the use of a rigorous randomized methodology.

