**Statistical Analysis**

We will measure the receipt of results as a proportion of those undergoing testing who receive their results before the onset of labor. We will compare the proportions between the 2 groups using the χ² test. We will calculate a satisfaction score for all study participants using the Decisional Conflict Scale which has been validated in many study populations. (20) We will compare mean satisfaction scores between the 2 groups using the Student t-test (if the distribution is parametric) or Wilcox rank-sum test (if the distribution is non-parametric). Lastly, we will conduct multivariate logistic regression to assess independent predictors using STATA SE8. We will test for interaction and stratify the multivariate analysis accordingly. We will conduct a strict intention-to-treat analysis. We will develop the data collection forms with the date and alphanumeric code on each page. Each variable will be named and coded. We will utilize a Microsoft ACCESS relational database. We will pretest the data management system with “dummy” data. We will promptly enter the data after collection and set criteria within the ACCESS database to minimize the likelihood of incorrect data entry. Once all data is entered, we will edit the database, checking for missing data, illogical data and outliers. We will log any changes made in the database during the editing process and freeze the final database before importing the data into statistical analysis software. We will then analyze and archive the database.

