**Sample Size**

Our sample size calculation was based on the primary outcome, decisional conflict score. Because this was a non-inferiority trial, the trial was designed to be able to exclude an actual difference between the abbreviated and standard counseling arms of greater than 5.625 (the non-inferiority margin) with respect to the mean decisional conflict score (DCS) in each group. To calculate our sample size, we used a type-I error rate (alpha) of 0.05 with an 80% power, a common standard deviation of 18.75 for the DCS, and a one-sided two group t-test of equivalence in means (equal n's) to arrive at 139 patients in each arm for a total of 278 participants. 20, 21 Assuming 75% participation as was seen in a 1997 study of the same patient population (i.e. those accepting enrollment and randomization), we will need to approach 371 women overall.

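### The only multivariable model named is logistic regression with no stated outcome: it cannot give an adjusted DCS difference to set against 5.625, and for testing uptake it would rest on about 19 to 20 untested women

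*Protocol*

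**What the plan says.** The Sample Size section identifies the endpoint: "Our sample size calculation was based on the primary outcome, decisional conflict score". The trial is sized to exclude a difference in mean score "greater than 5.625 (the non-inferiority margin"), using "a common standard deviation of 18.75 for the DCS", "we used a type-I error rate (alpha) of 0.05 with an 80% power", and "a one-sided two group t-test of equivalence in means (equal n's"), which gives 139 women per arm.

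The Statistical Analysis section compares the score between arms with a t-test or rank-sum test and compares proportions with a χ² test. It then adds: "Lastly, we will conduct multivariate logistic regression to assess independent predictors using STATA SE8". The next sentence is "We will test for interaction and stratify the multivariate analysis accordingly". No dependent variable is given for the model, and no linear model appears anywhere.

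The Study Design section lists six kinds of potential confounder to be measured: demographics, prior HIV testing, HIV knowledge, attitudes to testing, HIV test result, and provider type. On expected uptake, the Preliminary Studies section reports that "prenatal HIV testing uptake at SFGH has increased from 52% in 2003 to 93% as of April 2006".

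**The concern.** The trial's conclusion depends on a difference in means measured in DCS points. Logistic regression needs a binary outcome and returns an odds ratio, which has no counterpart to a 5.625-point margin. The one adjusted analysis in the plan therefore cannot provide an adjusted estimate for the primary question, and the covariates being collected cannot sharpen that estimate.

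Testing uptake is a natural binary outcome for the model, but at this site almost everyone is tested. The effective sample size of a logistic model is set by the rarer outcome, here the untested women. Six kinds of covariate, interaction tests and stratification driven by those tests would all draw on very few of them. The fitted odds ratios would then be imprecise and overfitted, and the strata could reflect chance.

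The covariate list brings two further difficulties. HIV test result does not exist for an untested woman, so it cannot enter an uptake model. In addition, both questionnaires described in the Study Design section follow counselling. If knowledge and attitudes are collected there, they are measured after the intervention, and adjusting for them could remove part of the arm effect.

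**Working it through.** **1. The plan's own figure.** Inputs from the Sample Size section: margin 5.625, SD 18.75, one-sided alpha 0.05, power 80%, true difference taken as 0.

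- n per arm = 2 × (1.645 + 0.842)² × (18.75 / 5.625)² = 2 × 6.18 × 11.11 ≈ 137.4, so 138 by the normal approximation.
- The exact noncentral-t calculation gives 139 (power 80.2%), as stated.
- This calculation is for an unadjusted two-group comparison. It does not use the multivariable model.

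**2. What a linear model would add for the DCS.** At 139 per arm the standardised distance to the margin is (5.625 / 18.75) × √(139 / 2) = 0.3 × 8.337 = 2.501, and power ≈ Φ(2.501 − 1.645) = 0.80. Adjusting for covariates that explain a share R² of the variance reduces the residual SD by √(1 − R²), so power ≈ Φ(2.501 / √(1 − R²) − 1.645). The documents give no R², so a range is assumed:

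| Assumed R² | 2.501 / √(1 − R²) | Power at 139 per arm |
|---|---|---|
| 0 | 2.50 | about 80% |
| 5% | 2.57 | about 82% |
| 10% | 2.64 | about 84% |
| 20% | 2.80 | about 88% |

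**3. Untested women available to an uptake model.** Expected number = 278 × (1 − uptake). The only uptake figure near the trial's setting is the clinic-wide 93%. Uptake among consenting participants, and in the abbreviated arm, is not given, so a range is shown. Six covariate groups at one term each, plus arm, make seven parameters. That is a minimum, because demographics will need more than one term.

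| Uptake | Untested women of 278 | Per parameter (7) |
|---|---|---|
| 90% | 27.8 | 4.0 |
| 93% | 19.5 (95% binomial range 12 to 28) | 2.8 |
| 95% | 13.9 | 2.0 |
| 98% | 5.6 | 0.8 |

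- Without HIV test result there are six parameters, and at 93% uptake 19.5 / 6 ≈ 3.2 per parameter.
- By the common rule of thumb of ten events per parameter, 19.5 women support about two parameters: arm plus one covariate.
- Seven parameters at ten each need 70 untested women, that is, uptake of 1 − 70 / 278 ≈ 75% or lower.
- If an interaction test led to two strata of equal size (an illustration), each would hold about 19.5 / 2 ≈ 9.7 untested women.

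**4. How badly such a model behaves.** In a simulation with seven parameters and assumed covariate effects (600 runs per setting), failed or extreme fits occurred in about 0.5% of runs at 93% uptake and about 36% at 98%. At 93% the problem is therefore mainly imprecision and overfitting. Outright breakdown becomes common only as uptake approaches 98%.

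**5. Receipt of results.** This is another possible binary outcome for the model. The documents give no expected rate for it, so the same calculation cannot be made.

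**The case against.** The strongest reply is that the protocol never assigns the logistic model to the DCS. The score has its own t-test or rank-sum test, the model comes in separately to look for predictors, and two binary outcomes (uptake and receipt of results) suit it. An unadjusted primary comparison is legitimate in a randomised trial, and the gain from adjustment depends on an R² that the documents do not supply. The covariates are listed as things to measure, not as the contents of one model. Covariate selection, penalisation and the number of interactions are commonly left to a statistical analysis plan, which is not at hand.

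Most of this stands, and it limits the point in three ways. A reader might infer that the DCS will be dichotomised and that the primary analysis will lose power. The documents do not support that: they give no cut-point, and the 80% power belongs to the unadjusted test. A reader might also infer that the uptake model will be unstable. At 93% uptake that is not shown. Nor does the text say that every listed covariate will enter a model for uptake.

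What the reply does not remove are two choices that the protocol makes itself. It names one class of multivariable model, and that class cannot address the primary endpoint on its own scale. It also states that the model will be stratified according to interaction tests. These are stated choices rather than details left open.

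**Conclusion.** The point holds as a criticism of the secondary, adjusted analysis. The protocol's only multivariable model cannot produce an adjusted mean difference comparable with 5.625. If used for uptake, it would have about 19 to 20 untested women at 93% (about 28 at 90%, about 6 at 98%). That is too few for the listed covariates together with stratification driven by interaction tests.

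The primary comparison, the 139 per arm and the 80% power are unaffected. The cost is overfitting and imprecision in the secondary model, and a modest amount of precision forgone on the primary estimate: power of about 82% to 88% in place of 80%, if baseline covariates explain an assumed 5% to 20% of the variance. The uptake figures assume that the clinic-wide rate roughly carries over to participants and that most of the listed covariates would be used. The protocol confirms neither. The change is worth making because it costs little; it is not needed to rescue the main result.

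**What to change.** - **DCS.** Add a linear regression of the score on arm plus a few prespecified pre-randomisation covariates that the trial already records, for example prior HIV testing, language and provider type. Report the adjusted mean difference with its one-sided 95% limit against 5.625.
- **Logistic model.** Name its dependent variable. If it is uptake, limit the model to arm plus one or two baseline factors, or use a penalised fit such as Firth's. Leave out HIV test result, and leave out knowledge and attitudes if they are measured after counselling.
- **Interactions.** Label them exploratory, and drop the rule that stratifies the model according to the tests. Report the overall arm effect whatever the tests show.

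This changes wording only: the data and sample size stay the same. The downside is that fewer exploratory predictors are examined.

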**Trial Protocol**

**Synopsis**

We propose a randomized controlled, non-inferiority trial to evaluate the effectiveness of two HIV testing strategies among 278 pregnant women seeking prenatal care at San Francisco General Hospital. The two strategies will include pretest/post-test counseling using prenatal care nurses and medical providers (control arm; current standard of care at San Francisco General Hospital [SFGH]) and an abbreviated pretest/post-test CDC recommended strategy using prenatal care nurses and medical providers (study arm). We hypothesize that the abbreviated CDC recommended strategy will be equally acceptable to patients as the standard strategy currently used. Eligible participants will include Spanish or English-speaking women seeking prenatal care at San Francisco General Hospital over the course of approximately one year. Eligible women presenting to SFGH physician or midwife prenatal clinics will be recruited, consented and randomized by study staff to either the standard or abbreviated testing strategy. The outcomes studied will be patient satisfaction and the proportion of study participants who undergo HIV testing. Satisfaction will be measured using the validated Decisional Conflict scale.

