**Study Design**

This will be a randomized controlled, non-inferiority trial comparing two HIV testing strategies among English and Spanish-speaking patients presenting for prenatal care at SFGH WHC over the course of approximately one year. Eligible participants will be randomized by study personnel to either standard HIV counseling and testing (control arm) or abbreviated counseling and testing (study arm). See Appendix 1. Participants will receive a standard prenatal HIV testing brochure, undergo one of two HIV counseling/testing strategies, submit blood for an HIV-1 antibody test, and will follow-up with their medical provider for HIV test results. Upon completion of counseling, participants will undergo a short, structured (Pre-test) questionnaire administered by study staff. Following testing and receipt of results, participants will complete a second (Post-test) structured questionnaire administered by study staff. Eligible women presenting to SFGH physician or midwife prenatal clinics will be recruited, consented and randomized by study staff to either the standard or abbreviated testing strategy. The outcomes studied will be patient satisfaction and the proportion of study participants who undergo HIV testing. Potential confounder variables to be measured will include demographic characteristics, prior HIV testing history, knowledge about HIV/AIDS, attitudes towards HIV testing, HIV test result, and type of provider (physician versus midwife).

All procedures will take place in SFGH Women’s Health Clinic. Time required of the subjects outside of routine prenatal care visits includes approximately 10 minutes for recruitment and randomization, 5-10 minutes for the pre-test questionnaire, and 5 minutes for the post-test questionnaire. If the patient is lost to follow-up and can no longer be reached upon visiting the clinic, the follow-up interview will be attempted to be conducted via telephone. We will specifically ask the participant permission on whether or not we can leave a simple message on her voicemail if she is lost to follow-up.

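### Strict ITT is the only analysis set named for this non-inferiority comparison, so cross-over in counselling could ease a false claim if the abbreviated strategy is truly worse

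*Protocol*

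**What the plan says.** The Study Design section opens with "This will be a randomized controlled, non-inferiority trial comparing two HIV testing strategies". Sample Size makes the decisional conflict score primary and requires the trial to exclude a difference in means "greater than 5.625 (the non-inferiority margin"), using a one-sided test at 0.05. Statistical Analysis commits to one analysis set: "We will conduct a strict intention-to-treat analysis".

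On delivery, the Synopsis describes the control strategy as "pretest/post-test counseling using prenatal care nurses and medical providers (control arm") and the new strategy as an "abbreviated pretest/post-test CDC recommended strategy using prenatal care nurses and medical providers (study arm"). It also identifies the control strategy as the hospital's current standard of care. Study Design sets randomisation at the level of the woman ("Eligible participants will be randomized by study personnel to either standard HIV counseling and testing (control arm) or abbreviated counseling and testing (study arm")) and puts both arms in one place: "All procedures will take place in SFGH Women’s Health Clinic".

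The protocol describes no separation of staff by arm and no check on which counselling was given. Its sample size has no allowance for cross-over; the only allowance is for 75% participation among women approached. The potential confounders listed for measurement in Study Design include provider type but not the counselling delivered.

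**The concern.** In a superiority trial, analysing women as randomised is cautious, because cross-over dilutes a real effect and makes it harder to demonstrate. In a non-inferiority trial the same dilution can work the other way. If the new strategy is truly worse, every woman who receives the other arm's counselling pulls the two means together, and the upper confidence limit is more likely to fall below the margin.

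This design gives cross-over an opening. The arms differ in how fully similar staff counsel, within one clinic, woman by woman. Full counselling is the existing routine, so staff must depart from it for each woman in the abbreviated arm.

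A finding of non-inferiority might then partly reflect women in both arms having received similar counselling. Nothing described in the protocol would let a reader tell. The second specific aim is an abbreviated counselling protocol for use in prenatal settings across the state, so a mistaken claim would carry beyond this clinic.

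**Working it through.** **Inputs from the protocol (Sample Size):** margin 5.625, common SD 18.75, one-sided alpha 0.05, power 80%, equal arms, 139 per arm (278 in total), 75% participation.

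**Input not in the protocol:** the cross-over rate. It is varied below as an assumption.

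**1. Reproduce the plan's figure.** With a true difference of zero, the normal approximation gives n per arm = 2 × (1.645 + 0.842)² × (18.75 / 5.625)² ≈ 137.4, rounded up to 138. The noncentral t calculation gives power 0.7998 at 138 and 0.802 at 139, so 139 per arm is confirmed. Also, 278 / 0.75 = 370.7, which gives the stated 371 women to approach. There is no arithmetic error.

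**2. Standard error of the difference.** SE = 18.75 × √(2/139) = 2.249.

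**3. Effect of cross-over on the ITT difference.** Let Δ be the true difference in means, with positive values meaning abbreviated counselling is worse. Let a be the fraction of abbreviated-arm women who receive full counselling, and b the fraction of control women who receive abbreviated counselling. If a crossed-over woman takes on the whole mean of the other strategy, the expected ITT difference is Δ(1 − a) − Δb = Δ(1 − c), where c = a + b.

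**4. False non-inferiority rate.** Set Δ = 5.625, the least favourable point at which non-inferiority should not be claimed, and hold the SD at 18.75. The chance that the one-sided 95% limit falls below 5.625 is Φ(−1.645 + c × 5.625 / 2.249). The equivalent threshold is 5.625 / (1 − c), the true difference that an ITT limit at 5.625 in effect excludes.

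| Total cross-over c (assumed) | Expected ITT difference | False non-inferiority rate | True difference in effect excluded |
|---|---|---|---|
| 0% | 5.625 | 5.0% | 5.625 |
| 10% | 5.063 | 8.2% | 6.25 |
| 20% | 4.500 | 12.6% | 7.03 |
| 30% | 3.938 | 18.6% | 8.04 |

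**5. When there is no inflation.** If Δ = 0, then Δ(1 − c) = 0 for every c. The ITT mean difference does not move and power stays at about 80%. If Δ is negative (abbreviated counselling better), dilution works against the new strategy.

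**6. Power of a per-protocol margin test at Δ = 0.** With c split evenly, each arm keeps 139(1 − c/2) women, and power is Φ(5.625 / SE′ − 1.645) with SE′ = 18.75 × √(2 / [139(1 − c/2)]). This gives 78.6%, 76.7% and 74.6% at c = 10%, 20% and 30%. If only one arm crosses over, the figures are 78.5%, 76.2% and 73.4%.

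**The case against.** **The SAP may deal with it.** Definitions of per-protocol sets often sit in a SAP, and none is at hand. A commitment to ITT does not forbid a supporting analysis, so it would be too strong to say that the trial has none. That stands. However, the word strict is a positive choice, and a SAP adding another set would have to be reconciled with it. A SAP also cannot use information that was never collected. Delivered counselling is absent from the variables that Study Design lists, although that list is of potential confounders and may not be the whole form.

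**The documents do not say that the same individuals counsel both arms.** A reader might infer it, but the Synopsis names only the same staff groups. Study Design refers to an appendix, not in the text at hand, that might say how delivery is organised. The point therefore rests on shared staff groups, one clinic and individual randomisation.

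**Cross-over does not always favour the new strategy.** This is another tempting reading, and step 5 shows that it is wrong. Inflation arises only when abbreviated counselling is truly worse. That is nevertheless the situation in which the type I error has to be controlled.

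**The size is assumed.** No cross-over rate is given, and the figures require a true difference exactly at the margin and all-or-none switching. They show sensitivity and are not evidence that cross-over will occur.

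**The remedy is partial.** The likelier contamination may be a slow convergence of counselling style, which a form field completed at the visit would miss. A per-protocol set would inherit that dilution and lose some of the protection of randomisation. This also stands. It argues for a supporting role for the per-protocol analysis, not for leaving it out.

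**Conclusion.** The point holds as an inexpensive improvement to the plan. ITT is defensible as the primary analysis, and the sample size is correct on its own inputs. The weakness is that ITT is the only analysis set the protocol names for a non-inferiority comparison in a setting where cross-over is plausible, with no stated record of what was delivered.

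If abbreviated counselling is worse by exactly the margin, total cross-over of 10%, 20% or 30% takes the nominal 5% error to about 8%, 13% or 19%. These are scenarios and rest on assumed rates, complete switching by the women concerned, and an SD of 18.75.

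A reader might go further and conclude that both ITT and per-protocol analyses must succeed before non-inferiority is claimed. The protocol does not compel that. It is a debatable trade-off that costs power, with per-protocol power already down to about 77% at 20% total cross-over split evenly, and the sample size makes no provision for it.

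**What to change.** - Keep ITT as the primary analysis.
- Add a field to the data form recording, for each woman, which counselling strategy was actually delivered.
- Unless the SAP already does so, prespecify a key supporting per-protocol analysis restricted to women who received the strategy they were assigned. Apply the same test as for ITT: the upper one-sided 95% limit of the difference in mean decisional conflict score against 5.625.
- Report the amount of cross-over by arm, and report and explain any discordance between the two analyses.

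The cost is one form field and one repeated analysis. The per-protocol set will be smaller and somewhat less powerful, and it is open to selection because it is not fully protected by randomisation, so it must be read beside ITT. It will not reveal gradual drift in counselling style, and the report should say so.
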